## Methods

### Patients

Female patients over the age of 18, with a recent diagnosis of breast cancer and scheduled for adjuvant treatment in the form of chemotherapy, radiation therapy and/or hormonal therapy are eligible for this study and will consecutively be included in the project. Patients will be recruited from three hospitals in the central part of Sweden (Uppsala, Gävle and Falun). Criteria for exclusion are an ongoing psychiatric condition or language deficiencies in Swedish. According to the power calculations, a total sample of 300 patients is necessary.

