### Design

The study is a prospective longitudinal intervention study with a stepped-care approach [13], where patients will be randomised to one of two interventions in the final stage of treatment. One of the key concepts in the stepped-care model is that the needs of the individual are matched to the appropriate level of care [13]. The first step is a low intensity intervention that is given to all patients. Patients who do not respond to this level are thereafter given more intensive treatment at later steps in the program. Since methods from CBT (cognitive behavior therapy) have already been shown not only to reduce the risk for PTSD [8] but also to have a positive effect on quality of life and psychological well being for patients with breast cancer [9,14], there is no control group in the study. All patients (n = 300) will receive the first level of the intervention program. All patients (estimated to n = 150) who continue to report stress symptoms after the first step of the intervention program will be given the chance to participate in the second step of the program. The second step includes randomisation to one of two treatments: a stress management group or individual stress management (See Figure 1). With this design it will be possible to study the prevalence of stress related symptoms as well as to study which factors predict which patients will be Clinically Significant Improved (CSI) with a basic level of education about stress management. In addition the study will help to identify those patients who need additional help and to compare the effects of individual and group interventions.

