### Data analysis

SPSS® ANOVA will be used to analyze differences between groups and for repeated measures over time for the continuous variables while nominal (categorical) variables will be tested with chi square (exact). Although not all the criteria for normal distribution are met by this selection the parametric tests are robust enough to be used. Patients’ levels of stress related symptoms will be categorized according to recognized cut-off points (See references in Table 1). A hierarchical linear regression analysis will be used to examine which variables predict stress symptoms and utilization of health care services as well as sick leave and return to work. Power calculations have been done for IES based on data from Support Project. On the basis of these conditions (power = 0.8, p = .05 and effect size = 0.59) at least 64 patients must be included in each group (i.e. a total of 128) patients) to detect a significant difference on IES.

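### The sample-size sentence is internally inconsistent: effect size 0.59 with 80% power needs about 47 patients per group, while the stated 64 is the answer for effect size 0.50

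*Protocol article*

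**What the plan says.** The Data analysis section of the protocol article bases the calculation on the Impact of Event Scale (IES), the primary outcome: "Power calculations have been done for IES based on data from Support Project". It then lists the inputs and presents the sample size as following from those conditions: "power = 0.8, p = .05 and effect size = 0.59) at least 64 patients must be included in each group", which it gives as 128 in total.

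The comparison is between the two randomised Step 2 formats (Design): "The second step includes randomisation to one of two treatments: a stress management group or individual stress management". The analysis is by ANOVA (Data analysis): "ANOVA will be used to analyze differences between groups and for repeated measures over time for the continuous variables".

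The Patients section refers back to the same calculation for recruitment: "According to the power calculations, a total sample of 300 patients is necessary". The Design section expects about 150 of the 300 to be eligible for Step 2.

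**The concern.** The sentence prints power, alpha, effect size and sample size together, and any three of these determine the fourth. Here they do not fit: 64 per group is well above what 0.59 requires, and it coincides with the familiar requirement for 0.50.

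This is the only justification given for the size of the randomised comparison on the primary outcome, and the recruitment target is attributed to it. As printed, a reader cannot reproduce the figure or tell which effect the authors were aiming at. That matters for judging how much loss the randomised stage can absorb. If 0.50 was the target, 128 is the minimum for analysis. If 0.59 was the target, 94 is enough.

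**Working it through.** **Inputs.** From Data analysis: power 0.80, alpha 0.05, effect size 0.59, stated n of 64 per group (128 in total). From Design: two groups; equal allocation follows from 64 + 64 = 128. Two assumptions, because the article is silent: alpha is two-sided, and 0.59 is a standardised mean difference *d* (difference in means divided by the SD). With two groups, between-group ANOVA is equivalent to the two-sample t test.

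**Step 1: try to reproduce the stated 64 at d = 0.59.**
Normal approximation: n per group = 2(z₀.₉₇₅ + z₀.₈₀)² / d² = 2(1.960 + 0.842)² / 0.59² = 2 × 7.849 / 0.3481 = 45.1, so 46.
Exact t test (noncentral t): 46.08, so 47 per group, 94 in total.
The stated figure is not reproduced: 64 / 47 = 1.36, so it is 36% too high.

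**Step 2: find the effect size that gives 64.**
At d = 0.50, the normal approximation gives 2 × 7.849 / 0.25 = 62.8, so 63. The exact t test gives 63.77, so 64 per group and 128 in total, matching both printed figures. Conversely, with 64 per group the smallest difference detectable with 80% power is d = 0.499.

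**Step 3: power actually provided (exact t test, two-sided 0.05).**

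| n per group | d = 0.50 | d = 0.59 |
|---|---|---|
| 47 | 67% | 81% |
| 64 | 80.1% | 91.2% |
| 75 (half of the expected 150, before any loss) | 86% | 95% |

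**Step 4: could another reading of the inputs give 64 at 0.59?**

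| Variant | n per group | Remark |
|---|---|---|
| One-sided alpha 0.05 | 37 | Widens the gap |
| Power 0.90 | 62 | Contradicts the stated 0.8 |
| Alpha 0.025 | 56 | Contradicts the stated .05 |
| Alpha 0.0125 (four-way Bonferroni) | 66 | Contradicts the stated .05 |
| Rank test, efficiency 0.955 to 0.864 | 50 to 55 | Not planned; still short |
| Three-group ANOVA, smallest f | 57 | There are two groups; still short |
| 0.59 read as Cohen's f | about 13 | Much further away |

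To get from 47 to 64 by inflation would need about 26% loss (47 / 0.74 = 63.5, so 64) or a design effect of 64 / 47 = 1.36. The article states neither.

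**The case against.** The best defence is that the missing link exists but is not printed. The 64 might include an allowance for loss or for clustering within the therapy groups. Or 0.59 might be scaled to the baseline SD while the test is on change scores. With a within-patient correlation of about 0.30 (an assumption; the article gives none), the SD of change is √(2 × 0.70) = 1.18 baseline SDs, and 0.59 / 1.18 = 0.50. These possibilities mean one cannot say for certain that 0.59 or 64 is itself a wrong number. They do not rescue the sentence, which presents 64 as the minimum that follows from the three listed inputs alone.

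A second objection is that the discrepancy does no harm. This largely stands. On either effect size, 64 per group reaches at least 80% power. About 75 per arm, before refusal and loss, exceeds both 47 and 64.

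A reader might also be tempted to go further in three ways that the article does not support:

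- **That 150 and 300 must be recalculated.** The Patients section does attribute 300 to the power calculations, but 150 is half of 300, in line with the hypothesis that half improve in Step 1. No step from 128 to 150 is shown. If 0.50 was meant, nothing changes; if 0.59 was meant, the totals are more than sufficient.
- **That 0.59 comes from the wrong Support Project comparison.** The article says only that the calculations used data from that project. It does not say that 0.59 is an observed between-arm effect, and the source contrast is detail that a condensed article may leave to the full protocol.
- **That the trial has either 80% power for 0.50 or 91% power for 0.59.** With 64 per group both statements are true at once. Only the intended target is unclear.

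**Conclusion.** The sentence is wrong as written. Its stated inputs require about 47 per group (94 in total), not 64 (128). The printed 64 fits an effect size of 0.50, and at 0.59 it delivers about 91% power. This rests on a two-sided test and on 0.59 being a standardised mean difference; a one-sided test or a Cohen's f reading makes the mismatch larger.

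The error is conservative. A reader might infer that the trial is underpowered, but the inconsistency alone does not show that. A reader might also infer that 0.59 is a misprint for 0.50. The exact match makes this plausible, but the article does not settle which figure is at fault. This is a reporting error in the justification for the primary comparison, not a defect in the design.

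**What to change.** Check the original calculation and rewrite the one sentence in Data analysis so that inputs and answer agree, using whichever of these is true:

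- effect size 0.50, 64 per group (128 in total), 80% power;
- effect size 0.59, 47 per group (94 in total), 80% power; or effect size 0.59, 64 per group, about 91% power;
- effect size 0.59 with 47 per group for analysis, raised to 64 by an allowance for loss or clustering, with the rate or design effect and the arithmetic shown.

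In each case, state that the test is two-sided (if it is) and that the effect size is a standardised mean difference. The cost is one corrected sentence and no additional patients. The planned totals of 150 and 300 can stay as they are.

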### Ethical considerations

The project has been approved the Regional Ethical Review Board in Uppsala 20090327, Diary number 2008/382. A written informed consent for participation in the study was obtained from participants. The interventions in the project will be provided by specially trained staff and supervised continuously so that any potentially harmful interventions can be detected early in treatment and corrected immediately. Filling in numerous questionnaires can be demanding. The questionnaires used in this study have been chosen with care, both in terms of length and number. However, if the number or length of questionnaires were to be further reduced it could make it difficult to reach any conclusions, which would reduce the value of this study for patients and grant-givers alike.

## Discussion

The interventions that are planned for in this project are directed towards symptoms that can make or break the course of illness for an individual patient. Hopefully the project will show that a stepped-care approach can help and support individual patients at the right level of care. All patients will receive stress management training. Those who require more help will receive additional treatment for their symptoms in the form of individual or group counselling. Health care and society may gain substantially from the planned intervention program, both in the form of individualized psychosocial support and reduced utilization of health care, preserved work capacity or a quicker return to work. The more intensive support will only be offered to those patients who show a clear need. For research purposes it is also important to increase what is known about stressors that are specific to women diagnosed with breast cancer and to develop interventions that are directed at these symptoms. This study will be conducted in three different counties in central Sweden which contributes to increased generalization and dissemination of the results of the study. This can lead to implementation of similar evidenced-based psychosocial care for cancer patients within a large geographical area.

Limitations of the study should be noted as well. The lack of a true control-group in step-2 can result in difficulties to interpret the effects of the stress-intervention. If there is a positive result, we cannot be absolutely sure that this effect would not be present in an untreated group. However, we consider not to have a untreated control since methods from CBT (cognitive behavior therapy) have already been shown not only to reduce the risk for PTSD [8] but also to have a positive effect on quality of life and psychological well being for patients with breast cancer [9,14]. It would not be ethical to withdraw patients in need from a treatment that has been found effective.
